## Abstract

**Background:**

A key strategy in improving care for people with chronic obstructive pulmonary disease (COPD) is the provision of pulmonary rehabilitation programmes. Pulmonary rehabilitation programmes have been successful in improving patients' sense of dyspnoea and Health Related Quality of Life. However, the effectiveness of structured education pulmonary rehabilitation programmes delivered at the level of the general practice on the health status of people with COPD remains uncertain and there is a need for a robust and fair assessment of this. The PRINCE study will evaluate the effectiveness of a Structured Education Pulmonary Rehabilitation Programme (SEPRP), delivered at the level of the general practice, on the health status of people with COPD.

**Methods/Design:**

The PRINCE Trial is a two-armed, single blind cluster randomised trial conducted in the primary care setting in Ireland. Randomisation to control and intervention is at the level of the General Practice. Participants in the intervention arm will receive a SEPRP and those allocated to the control arm will receive usual care. Delivery of the SEPRP will be by a practice nurse and physiotherapist in the General Practice (GP) site. The primary outcome measure of the study will be health status as measured by the Chronic Respiratory Questionnaire (CRQ). Blinded outcome assessment will be undertaken at baseline and at twelve-fourteen weeks after completion of the programme. A comparison of outcomes between the intervention and control sites will be made to examine if differences exist and, if so, to what extent between control and experimental groups. Sample size calculations estimate that 32 practices with a minimum of 10 participants per practice are required, in total, to be randomised to control and intervention arms for power of at least 80% with alpha levels of 0.05, to determine a clinically significant change of 0.5 units in the CRQ. A cost effectiveness analysis will also be conducted.

**Discussion:**

The results of this trial are directly applicable to primary care settings in Ireland. Should a SEPRP delivered by practice nurses and physiotherapists in primary care be found to be effective in improving patients' sense of dyspnoea and HRQoL, then the findings would be applicable to many thousands of individuals in Ireland and beyond.

**Trial registration:**

ISRCTN: ISRCTN52403063

## Background

By 2030, COPD will rank seventh in the worldwide burden of disease [1] and will be the third most frequent cause of death [2]. Few countries, however, have good population-based data on COPD and estimates of the prevalence of COPD differ widely, depending on the criteria that are used. Halbert et al. [3] report prevalence rates of 0.23% to 18.3% in Europe and North America with typical rates of 4 to 10%. The Burden of Obstructive Lung Disease (BOLD) initiative found that the prevalence rates of stage II or higher COPD was 10.1% greater than that reported in previous studies suggesting that prevalence rates of COPD may be underestimated [4]. There is little accurate data available on the prevalence of COPD in Ireland. A useful comparison may, however, be made with data from the United Kingdom where it is estimated that the rate of COPD in the population attending GPs ranges from 2% - 4%.

COPD is also the leading cause of workdays lost in the European Union [5]. In Ireland, the Economic and Social Research Institute [6] found that 20% of inpatient hospital bed days were due to COPD and in those aged over 65 years, COPD accounted for nearly a third of respiratory inpatient cases. This implies that if illness progression can be delayed and acute exacerbations of COPD prevented or reduced then significant alleviation of the economic and clinical burden could be achieved [7,8].

One of the key strategies in improving care for people with COPD is the provision of pulmonary rehabilitation (PR) programmes. PR programmes utilise a multidisciplinary approach and typically consist of a patient assessment, exercise training, education and psychosocial support [9]. They have been successful in improving patients' sense of dyspnoea and Health Related Quality of Life (HRQoL) [10-12]. PR programmes emphasise self-care and self-management. However, the extent to which these programmes meet the criteria for a structured education programmes [13] is unclear. Structured education programmes typically consist of a clear philosophy and a written, structured curriculum and include transparent quality assurance mechanisms. They are delivered by educators who have been trained to deliver the programme. Such programmes are more effective in promoting self-management in chronic conditions than unstructured education programmes [13].

PR programmes have been predominantly hospital or home based, although provision in the primary health care setting has been recommended [14,15]. To date, only one trial evaluating the effects of pulmonary rehabilitation on exercise tolerance and quality of life in people with COPD in the primary care setting has been identified [16]. This study included participants with asthma (n = 23) and COPD (n = 43). The pulmonary rehabilitation programme was delivered by a physiotherapist and included exercise classes, breathing techniques and relaxation activities. Of the 99 participants randomised, 23 subsequently withdrew and their outcomes were unavailable for analysis. Of those remaining, outcome data on quality of life (QoL) as measured by the dyspnoea, fatigue, emotion and mastery components of the Chronic Respiratory Disease Questionnaire (CRDQ) are available for only 23 participants. This study concluded that pulmonary rehabilitation for patients with COPD or asthma delivered in local practices improves exercise tolerance and quality of life.

The effectiveness of structured education pulmonary rehabilitation programmes delivered at the level of the general practice on the health status of people with COPD remains uncertain and there is a need for a robust and fair assessment of this. The PRINCE study will provide this assessment and will also give people with COPD an opportunity to voice their experiences of living with COPD and their approach to self-management.

Our proposed intervention, a structured education pulmonary rehabilitation programme, is delivered at the level of the general practice and is provided to a group of people with COPD rather than to individual patient participants. Therefore, the proposed trial is clustered at the GP practice level.

## Aim

The primary aim of the PRINCE study is to evaluate the effectiveness of a structured education pulmonary rehabilitation programme (SEPRP), delivered at the level of the general practice, on the health status of people with COPD. The trial has four main objectives:

1. To develop a comprehensive SEPRP specifically orientated toward delivery by GP practice nurses to people with COPD in their local communities.

2. To evaluate the effectiveness of the SEPRP within the context of a cluster randomised trial.

3. To understand participants' perceptions and experiences of 'COPD', its impact on their lives and their approach to self-management.

4. To evaluate the cost effectiveness of the provision of a SEPRP for people with COPD.

## Methods

## Design

The PRINCE Trial is a two-group, single blind cluster randomised trial conducted in the primary care setting in Ireland. Randomisation to control and intervention is at the level of the General Practice. Effective randomisation of a sufficiently large sample of participants to control and experimental groups ensures that there are no systematic differences between control and intervention groups in known (e.g. motivation) and unknown factors that may affect the outcome [17]. Participants allocated to the intervention group will receive a SEPRP and those allocated to the control group will receive usual care. Delivery of the PR programme will be by a practice nurse and physiotherapist in GP sites. Blinded outcome assessment will be undertaken at baseline and at twelve-fourteen weeks after completion of the programme. A comparison of outcomes between intervention and control sites will be made to examine if differences exist and, if so, to what extent between control and experimental groups. Randomisation to the PRINCE study began in September, 2009 and outcome assessment is due to end in February 2011.

## Eligibility Criteria

### Participants: GP practices (Clusters)

GP practices across the North Western, Western and Midland Health Service Executive (Ireland) regions who meet the following eligibility criteria are eligible to participate:

1. Supported by a practice nurse;

2. Practice supported by a computerised patient (medication recording) system;

3. Commitment on the part of the practice team to participate in the proposed study;

4. Have a patient population of more than 2500;

5. Participation by a minimum of 10 consenting patients meeting the eligibility criteria.

### Participants: Patients

Primary health care in Ireland is relatively under resourced and is characterised by poor infrastructure and limited interdisciplinary teamwork [18]. General Practitioners tend to operate independently to other primary health care services leading to a fragmented service delivery. Hence, most primary health care settings in Ireland have not implemented a strategy to proactively diagnose COPD as a part of routine practice. For this reason, potential patient participants will have either an existing diagnosis or be suspected of having COPD. COPD will be suspected when patients are receiving drug treatment for respiratory conditions, have a history of tobacco use, a chronic cough, regular sputum production, frequent winter bronchitis, breathlessness or any combination of these. Presence of COPD will be confirmed at baseline assessment by spirometry.

Diagnosis is confirmed with a post Bronchial Dilator FEV1/FVC ratio of less than 70%* unless BMI > 30 in which case FEV1/FVC ratio > 70% are acceptable provided other criteria are fully met and with a post bronchial dilator predicted value of FEV1 ≥ 30% and ≤ 80% (after Global Initiative for Chronic Obstructive Lung Disease (GOLD) 2008 [14]). The decision to adjust the spirometry inclusion criteria for individuals with a BMI > 30 is based on research undertaken by Wannamethee et al [19] who demonstrated that BMI was positively associated with FEV1:FVC.

Patients must be able to converse in and read English as initial delivery of the SEPRP will only be available in English. Patients must also understand the study and give informed consent. Patients will not be excluded if they have previously attended pulmonary rehabilitation programmes and all patients will remain under the care of their GP and/or respiratory physician.

Patients will be excluded from the study if they possess any significant underlying co-morbidities or mental health problems (based on the recorded judgement of practice staff), which are likely to impair their capacity to successfully participate in or assimilate new information as part of the rehabilitation programme or which may pose a risk to their health. Further detail on patient eligibility assessment is provided in Table 1.

**Table 1 T1:** Patient exclusion criteria

**History of**	**Currently:**
• Unstable cardiovascular disease	
ο unstable angina	Suspected or on treatment of relevant and/or current infectious disease (e.g. TB)
ο unstable aortic valve disease	• In the 3^rd ^Semester of Pregnancy
ο unstable pulmonary hypertension	• Haemoptysis of unknown origin
• Pneumothorax	
• Thoracic or Cerebral Aneurysms	**Having had within:**
• Musculoskeletal or neurological disorders that prevent gentle exercise	1 Month:
• Severe cognitive impairment	• Myocardial infarction^3^
• Severe psychotic disturbance	• Eye Surgery
• Detached Retina	3 Months
• Relative contraindications include	• Abdominal or thoracic surgery
ο a'resting heart rate of more than 120^3^	
ο a'systolic blood pressure of more than 180 mm Hg	
ο a'diastolic blood pressure of more than 100 mm Hg	

## Interventions

### Control Group (usual care)

The control group will receive 'usual care'. While the research team acknowledge the complexity and potential heterogeneity of 'usual care', substantial effort will be made to describe clearly the components of 'usual care' for COPD patients through information gathered from structured interviews with GPs, Practice Nurses, documentary analysis of participants health records and through interviews with participants. Practice nurses in the control group will be offered the SEPRP following the completion of post-programme data collection.

### Experimental Intervention

The experimental group will receive the SEPRP, which focuses on improving the self-management skills of persons with COPD. Structured education programmes are defined as planned programmes that are: "...comprehensive in scope, flexible in content, responsive to an individual's clinical and psychological needs and adaptable to his or her educational and cultural background" [13] (pg 27).

Across the literature it is clear that structured education should aim to: empower, inform and support self-management skills. The Department of Health [20] suggests that the aim of education is to improve knowledge and skills, enabling the person to take control of their own condition and to integrate self-management into their daily lives. They suggest that a supported self-care service model is most appropriate to chronic disease management. NICE [13] identify five key criteria for high quality structured education programmes (i) programmes should have a structured written curriculum (ii) a patient centred philosophy (iii) be delivered by trained educators (iv) be quality assured and (v) audited. The SEPRP was developed in accordance with these key criteria and in consultation with people with COPD, experts in pulmonary rehabilitation, general practitioners and practice nurses. The SEPRP was also informed by a detailed analysis of the literature in relation to pulmonary rehabilitation programmes.

The programme has been reviewed and validated by educational experts who were asked to focus on adult learning and empowerment and experts in pulmonary rehabilitation and COPD who were asked to focus on the appropriateness and comprehensiveness of content. The SEPRP has a course philosophy, a detailed curriculum, course materials and a training programme for all educators. It is founded on the principles of empowerment, self-efficacy and behavioural change theory and its development was guided by the Stages of Change/Transtheoretical Model of Behaviour Change [21]. Central to the programme is empowering people with COPD to manage their care well; consequently the programme delivery adopts a patient-centred approach with a focus on priority setting and problem solving. It consists of an eight-week programme with a two-hour session each week (16 hours total duration) delivered jointly by a practice nurse and physiotherapist. An overview of programme content is presented in Table 2.

**Table 2 T2:** Content of SEPRP

Week	Content	Educator
**Week 1**	Setting the scene	Practice Nurse
	Introduction to exercise	Physiotherapist

**Week 2**	Managing medications	Practice Nurse
	Exercise programme	Physiotherapist

**Week 3**	Exercise programme	Physiotherapist
	Exercise programme	Physiotherapist

**Week 4**	Managing breathlessness	Practice Nurse
	Exercise programme	Physiotherapist

**Week 5**	Knowing and managing your symptoms	Practice Nurse
	Exercise programme	Physiotherapist

**Week 6**	Recognising and managing acute exacerbations	Practice Nurse
	Exercise programme	Physiotherapist

**Week 7**	Exercise programme	Physiotherapist
	Managing stress and anxiety	Practice Nurse

**Week 8**	Exercise programme	Physiotherapist
	Where to now?	Practice Nurse

Support following the intervention is thought to be highly significant in adherence to the programme principles [22]. For this reason, practice nurses will provide ongoing advice and support to participants as required throughout the intervention. In addition, participants in the intervention will also be followed-up formally at 4 weeks and at 12-14 weeks after completion of the SEPRP.

The 4-week follow up is by telephone and aims to provide positive reinforcement to those adhering to the programme, identify any barriers preventing participants from adhering to the programme and discuss strategies to overcome these. At the 12-14 weeks follow up, participants will be asked to attend a 1-hour group session. This session will be delivered by the practice nurse. It builds on the eight-week structured education programme and aims to further empower inform and support persons with COPD to continue self-managing their COPD. Similar to the eight-week structured education programme, this follow up programme is underpinned by the principles of adult learning, an empowerment philosophy and the transtheoretical model of change. The focus of this programme is to facilitate clients to self evaluate their progress, appraise their achievements, problem solve and plan for the future.

It should be noted that we are not seeking to evaluate individual components of SEPRP but rather the entire programme. If there is a beneficial effect in outcomes for participants in the intervention arm we will be able to conclude that SEPRP is effective but will not be able to conclude what specific components of SEPRP contributed most to such effectiveness.

#### Practice Nurse Preparation Programme

Practice Nurses will attend a three day Practice Nurse Preparation Programme (PNPP) to prepare them to deliver the SEPRP.

The programme has four main components: (1) understanding the philosophy of the SEPRP, (2) principles of adult learning and effective management of small groups, (3) an introduction to programme materials and approaches to its implementation and (4) assessment of competence in delivery. Sessions are interactive and geared towards meeting participants' learning goals and needs. This programme was reviewed and validated by outside experts and was also piloted. The PNPP will be delivered in two stages. The initial two-days will focus on preparing practice nurses to deliver the SEPRP and on building confidence (Components 1, 2, 3). On the third day, held a week later, participants will role play delivering to their peers an assigned element of the structured education programme (Component 4). The research team will observe these presentations and feedbacks to each participant on their performance including their adherence to lesson plans and activities within the SEPRP curriculum. Providing participants with an opportunity to present a segment of the SEPRP will increase their confidence and skills for delivering the SEPRP. To ensure standardisation of programme content and delivery, members of the research team will deliver all PNPP training programmes. Practice nurses will be audited when delivering the SEPRP programmes in weeks 4 or 5 to ensure adherence to programme principles and content. An action plan will be developed and followed up as required.

#### Physiotherapist Preparation Programme

Physiotherapists will attend a one-day Physiotherapist Preparation Programme (PPP) focused on preparing physiotherapists to deliver the structured education programme. Programme content aims to prepare participants to: (1) understand the philosophy of the SEPRP, (2) understand and apply the principles of adult learning and effective management of small groups, (3) understand programme materials and approaches to its implementation and (4) deliver the exercise component of the programme as planned. Sessions will be interactive and geared towards meeting participants' learning goals and needs. There are 10 exercise stations each of 3 minutes duration focused on building exercise capacity, and tailored to each participant's individual needs. These exercises will also be repeated at home and recorded by participants in a home exercise diary.

Again to ensure standardisation of programme content and delivery, members of the research team will deliver all PPP programmes. Physiotherapists will also be audited in their facilitation of the SEPRP programmes in weeks 4 or 5 to ensure adherence to programme principles and content. Similar to the PNPP, an action plan will be developed and followed up if required.

All educators (practice nurses and physiotherapists) will be supported in the delivery of the programme over the eight weeks by having recourse to members of the research team for purposes of clarification on training materials and in identifying sources of information in response to specific patient queries.

## Outcome measures

Outcome measures will be collected from participants in both intervention and control groups at baseline (following consent, prior to randomisation and group allocation) and at 12-14 weeks post completion of the 8-week programme or at an equivalent time for the control group. We acknowledge that a longer follow-up period would be desirable but funding does not permit follow-up beyond this.

Each participating practice will be assigned a Research Assistant responsible for outcome assessment on all participating patients within that practice. To enhance the quality of measurements, all Research Assistants will undergo a one-day Research Assistant Preparation Programme consisting of:

i) Training on the procedures and protocols surrounding the delivery, assessment and recording of all outcome measurements;

ii) Discussion on adverse events and their management;

iii) Simulated completion of all data collection instruments and forms;

iv) Basic Life Support training (for those requiring certification);

### Primary

The primary outcome measure of the study will be health status as measured by the Chronic Respiratory Questionnaire (CRQ) [23]. This instrument was developed following interviews with people who had COPD [23]. The questionnaire has four domains: dyspnoea, fatigue, emotional function and mastery.

The validity and reliability of this tool was first investigated by Wijkstra et al. [24] who concluded that the CRQ was a valid and reliable tool. This conclusion was also confirmed by Curtis and Patrick [25] who found that the CRQ was reliable, valid and responsive to change. In addition, they claim that the CRQ is more sensitive to change than other generic health status instruments.

### Secondary

1. Incremental Shuttle Walking Test;

2. Self-Efficacy for Managing Chronic Disease 6-Item Scale [26];

3. Economic analysis specific:

a) EuroQol EQ-5D [27];

b) Utilisation of health care Service Utilisation of health care Service. For variables, i to v, we are dependent on practice notes for their determination. Based on our previous experience [28,29] we consider these to be reliable and valid:

i) Hospital admissions/length of stay;

ii) Attendance at the emergency department;

iii) Outpatient attendances;

iv) Attendance at/by GP;

v) Attendance at/by Practice Nurse;

vi) Attendance at/by Public Health Nurse;

vii) Attendance at/by Physiotherapy;

viii) Attendance at/by Social Worker;

ix) Attendance at/by Dietician;

x) Outpatient attendances;

xi) Attendance at/by consultant;

xii) Utilisation of Home help;

### Demographic variables

Data will be collected from each patient participant on current medication use, smoking history, education level, marital and employment status, level of social engagement and level of support with activities of daily living.

## Sample Size Estimation

We used methods for standard sample size estimates for trials that randomised at the level of the individual [30] adjusting for clustering by inflating sample size estimates by the design effect given by $1+(\bar{n}-1)\rho$, where $\bar{n}$ is the average cluster size, and ρ is the estimated intraclass correlation coefficient (ICC) [31]. Sample size estimates are based on the primary outcome of health status as measured by the CRQ [23], expressed as the mean rate difference between intervention and control groups.

Previous work suggests 0.5 as the minimal clinically important mean difference for all four dimensions of the CRQ [32] and estimates of standard deviations of 1.145 (given as arithmetic mean of 0.88, 1.06, 1.24 and 1.40 for the Dyspnoea, Fatigue, Emotion and Mastery dimensions of the CRQ respectively) [33]. Using these values and the upper value of 0.05 from a range of ICC values identified within studies involving the older person in primary care, [34] calculations indicate that 32 practices with a minimum of 10 participants per practice are required, in total, to be randomised to control and intervention arms for power of at least 80% with alpha levels of 0.05. This allows for participant loss to follow-up of 20% plus a loss of 4 practices. ICC values lower than 0.05 would increase the power of the study.

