## Quantitative Analysis

The analysis will be based on the GP Practice with the patient as the unit of analysis whilst accounting for the intracluster correlation coefficient. Analyses will be by intention to treat. Quantitative data will be analysed, in aggregate, using The Statistical Package for the Social Sciences (SPSS, v17) and R ([37], 2.11). Data will be entered into SPSS, coded, cleaned and locked before any analyses are made. Only members of the research team who needed access to the database to fulfil their roles within the study were granted access to the database. Funders did not have access to the database at any time. Demographic characteristics of the practices and the participants within the practices will be described using percentages, measure of central tendency (means or medians) and measures of variation (standard deviations or ranges). Comparability of randomised groups by socioeconomic and other categorical baseline variables will be by the chi-square (*X*^2^) test.

Whilst every effort will be made to exclude all confounders at the design phase of the study, this is not always possible. The analysis of data will therefore include the search for and control of nuisance variables for which adjustments had not been made. In particular, a mixed effects model will be used to model the longitudinal change in the mean scores for each of the four dimensions of the CRQ primary response while adjusting for explanatory variables and baseline CRQ as needed and incorporating random effects to model the homogeneity within cluster and the correlation within patient across time. The Akaike information criterion (AIC), for linear mixed-effects models in the analysis of clustered data, will be used to decide between candidate models [38]. The significance level will be set at α = 0.05 for all analyses.

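### The 80% power claim uses an SD averaged over the four CRQ dimensions, but each dimension is analysed separately; on the plan's own inputs Emotion has about 74% and Mastery about 63%

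*Protocol article*

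**What the plan says.** The primary outcome is health status measured by the CRQ, which has four domains (Outcome measures, Primary). Sample Size Estimation takes one target difference for all of them: "Previous work suggests 0.5 as the minimal clinically important mean difference for all four dimensions of the CRQ". For variability it uses "estimates of standard deviations of 1.145 (given as arithmetic mean of 0.88, 1.06, 1.24 and 1.40 for the Dyspnoea, Fatigue, Emotion and Mastery dimensions". The ICC is "the upper value of 0.05 from a range of ICC values identified within studies involving the older person in primary care". The result is 32 practices with at least 10 patients each, "to be randomised to control and intervention arms for power of at least 80% with alpha levels of 0.05", after allowing for 20% patient loss and the loss of four practices. The Abstract repeats the claim, describing the power as sufficient "to determine a clinically significant change of 0.5 units in the CRQ".

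The Quantitative Analysis section then plans a mixed model "to model the longitudinal change in the mean scores for each of the four dimensions of the CRQ primary response", adjusting for baseline CRQ where needed, with a significance level of 0.05 throughout. It names no total or mean CRQ score for analysis and gives no dimension priority.

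**The concern.** Power depends on the SD of the variable that is tested. Four variables are tested, with SDs from 0.88 to 1.40, and the calculation uses a fifth value that none of them has. Because the target difference is 0.5 for every dimension, averaging the SDs credits the less variable dimensions' precision to the more variable ones. The claim of at least 80% then understates power for Dyspnoea and Fatigue and overstates it for Emotion and Mastery.

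What is at stake is how a null result is read. Someone relying on the Abstract would take a non-significant Mastery result as fairly good evidence against a 0.5-unit benefit. On the plan's inputs, such a benefit would be missed about 37% of the time (100 − 63.3).

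**Working it through.** **Inputs, all from the article.** Difference 0.5; SDs 0.88, 1.06, 1.24 and 1.40, mean 4.58/4 = 1.145; ICC 0.05; alpha 0.05 (sidedness is not stated; two-sided is assumed, and it reproduces the plan); 1:1 allocation; 32 practices of 10. After the stated losses this is 28 practices (14 per arm) of 8, or 112 patients per arm.

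**Reproducing the plan.** Design effect = 1 + (8 − 1) × 0.05 = 1.35.

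Patients per arm without clustering = 2 × (1.96 + 0.8416)² × 1.145² / 0.5² = 82.3. Multiplied by 1.35 this is 111.1, and divided by 8 it is 13.9, so 14 practices per arm. That is 28 in total, and adding 4 gives 32, as stated.

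Power: SE = SD × √(2 × 1.35/112). At SD 1.145, SE = 0.1778 and 0.5/SE = 2.812, so power = Φ(2.812 − 1.96) = 80.3%. The largest SD that keeps 80% here is 1.149. Emotion and Mastery both exceed it.

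**Each dimension with its own SD, same losses and ICC.** The last column uses a noncentral t with 28 − 2 = 26 degrees of freedom.

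| Outcome | SD | SE | 0.5/SE | Power, normal | Power, t |
|---|---|---|---|---|---|
| Dyspnoea | 0.88 | 0.1366 | 3.659 | 95.5% | 94% |
| Fatigue | 1.06 | 0.1646 | 3.038 | 86% | 83% |
| Emotion | 1.24 | 0.1925 | 2.597 | 73.8% | 71% |
| Mastery | 1.40 | 0.2174 | 2.300 | 63.3% | 60% |
| Averaged SD | 1.145 | 0.1778 | 2.812 | 80.3% | 77% |

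**How far the shortfall depends on the losses and the ICC (normal approximation).** The design effect is 1.45 with 10 per practice, 1.14 with 8 per practice at ICC 0.02, and 1 at ICC 0.

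| Scenario | Emotion | Mastery |
|---|---|---|
| Stated losses, ICC 0.05 (28 × 8) | 73.8% | 63.3% |
| Patient loss only (32 × 8) | 79.3% | 69.1% |
| Practice loss only (28 × 10) | 80.0% | 69.9% |
| No loss (32 × 10) | 85.0% | 75.6% |
| Stated losses, ICC 0.02 | 80.7% | 70.6% |
| Stated losses, ICC 0 | 85.5% | 76.2% |

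With t, Emotion has 82.6% with no loss but 77.7% at ICC 0.02 with the stated losses. Mastery passes 80% only if both assumptions are relaxed together. With no loss and ICC 0, SE = 1.40 × √(2/160) = 0.1565, 0.5/SE = 3.19 and power is about 89%. That is far from the conditions under which the article makes its claim.

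**The case against.** **No sum is wrong.** The mean of the four SDs is 1.145 and the 32 practices follow from it. The article shows the averaging and all four SDs openly. This stands: the fault is the choice of input, not the arithmetic.

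**The planned model may do better than the unadjusted calculation.** It allows adjustment for baseline CRQ and models correlation within patient over time. If the quoted SDs are for follow-up scores, the residual SD is SD × √(1 − r²), where r is the baseline-to-follow-up correlation. Bringing it down to 1.149 needs r of about 0.38 for Emotion and 0.57 for Mastery (0.45 and 0.61 with t). These correlations are assumptions. The article gives none, does not say whether its SDs are for change or follow-up scores, makes the adjustment conditional, and takes no credit for it in the sample size. So a reader might infer that the trial is definitely underpowered for two dimensions, and the document does not support that. It supports only that the stated claim fails on the stated inputs.

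**The Emotion figure is a cautious case.** It combines the upper ICC, both kinds of loss and the minimum practice size. This also stands in part: the Emotion shortfall disappears with full retention or a low ICC. The article nevertheless makes its claim after exactly those losses and at that ICC.

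**A single CRQ score may have been meant.** For the mean of the four dimensions, 1.145 is an upper bound on the SD, reached only if they correlate perfectly. With an assumed correlation of 0.5 to 0.7 between dimensions, the SD would be about 0.91 to 1.01 and power 94% to 89% (about 93% to 87% with t), so the plan would be conservative. But the analysis section names the dimensions, not a score.

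**The t distribution is a refinement.** The article fixes no degrees-of-freedom method, and 26 is an assumption. The conclusion does not depend on it.

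**Conclusion.** The point holds in a limited form. The article's claim of at least 80% power does not carry over to two of the four dimensions it analyses as primary. At the stated ICC and losses, two-sided 0.05 and no baseline adjustment, power is about 74% for Emotion and 63% for Mastery (71% and 60% with t). Dyspnoea and Fatigue are above 80%.

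The Mastery shortfall is the firmer of the two: it survives removing all losses, or setting the ICC to 0, taken one at a time. The Emotion shortfall is conditional on the stated losses and ICC.

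A reader might also infer that more practices must be recruited. With the same method and loss allowances, 80% would take 38 practices for Emotion (96.5 × 1.35/8 = 16.3, so 17 per arm, plus 4) and 46 for Mastery (123.1 × 1.35/8 = 20.8, so 21 per arm, plus 4). The document does not promise 80% for every dimension in so many words, and the unknown gain from baseline adjustment means these counts cannot be called necessary. The defect is in what is claimed, and nothing here biases the treatment estimate.

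**What to change.** Restate the power sentence in the Abstract (Methods/Design) and in Sample Size Estimation per dimension, each with its own SD, preferably allowing for the small number of practices. For example: *With 28 practices of 8 patients after the allowed losses, an ICC of 0.05 and a two-sided 0.05 level, power to detect 0.5 units is about 94% for Dyspnoea, 83% for Fatigue, 71% for Emotion and 60% for Mastery (t distribution, 26 degrees of freedom). These figures are unadjusted; adjustment for baseline CRQ may raise them by an amount not estimated here.* If the normal approximation is kept, the figures are 95.5%, 86%, 74% and 63%, and the sentence should say so.

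Do not enrol more patients on this account. Do not adopt a mean CRQ score as primary to rescue the claim: the Design section dates the start of randomisation to September 2009, and the power of such a score would rest on a correlation the article does not give.

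The cost is two sentences and a less favourable figure for Emotion and Mastery.
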